## **3. Safety analyses**

As this research is part of the research involving the human "at risk and minimal constraints" (category 2 in Jardé Law), and in accordance with the regulations in force, it will be up to the investigator to declare any serious adverse event that occurred during the investigations according to the internal procedure of declaration of a serious adverse event associated with the care of his institution. The sponsor will conduct study quality monitoring. The project can be audited by the French competent authority in case of non-respect of the safety or the rights of the participant.

Adverse event: ANY noxious or undesirable event experienced by a participant during the trial, whether or not considered related to the intervention should be considered as an adverse event (AE).

Serious adverse event: A serious adverse event (SAE) has to be reported to the sponsor within the 48 hours of its occurrence. SAE is an adverse event that is: Fatal (even if not related to the disease); Life-threatening; Significantly, persistently or permanently disabling ; Requiring intervention to prevent permanent impairment or damage ; Any event that could be considered as potentially harmful ; Any event medically accurate according to the investigator's judgment.

These serious adverse events will be cautiously reported in the CRFs.

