### ***C. Clinical trials vigilance***

This research belongs to research involving human subjects with minimum risks and constraints, and in compliance with legislation in force, it is the investigator's liability to report any serious adverse event occurring during investigations according to the internal procedure for reporting a serious adverse event associated with healthcare in his/her institution.

The investigator must also specify that the patient is included in a clinical trial and accurately identify the name of the trial.

Indeed, for this category of research there is no longer any specific vigilance of the trial for the sponsor (art L1123-10 CSP, last paragraph).

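### Two unreconciled SAE reporting routes and two open-ended SAE criteria mean that SAE counts may differ between sites and investigators

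*Combined protocol and SAP*

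**What the plan says.** **SAP, VI.E.3 Safety analyses.** The section gives two instructions. It first asks the investigator to "declare any serious adverse event that occurred during the investigations according to the internal procedure of declaration of a serious adverse event", meaning the institution's own procedure for events linked to care. It then adds: "A serious adverse event (SAE) has to be reported to the sponsor within the 48 hours of its occurrence". On recording it says: "These serious adverse events will be cautiously reported in the CRFs".

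An adverse event is "ANY noxious or undesirable event experienced by a participant during the trial, whether or not considered related to the intervention". The SAE list has four specific criteria (fatal, life-threatening, disabling, needing intervention to prevent lasting damage) and two general ones: "Any event that could be considered as potentially harmful" and "Any event medically accurate according to the investigator's judgment".

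**Protocol, IX.C Clinical trials vigilance.** Here "it is the investigator's liability to report any serious adverse event occurring during investigations according to the internal procedure for reporting". The investigator must state in that declaration that the patient is in a trial and name the trial. The reason given is that "for this category of research there is no longer any specific vigilance of the trial for the sponsor". The section mentions no report to the sponsor, no 48-hour limit and no CRF entry.

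**The concern.** A site that works from IX.C would make an institutional declaration and stop there. A site that works from the later sentences of VI.E.3 would also notify the sponsor and complete the CRF. Section III.F describes seven institutions across Lyon, Marseille and Paris, each presumably with its own procedure, so the route affects which events reach the trial database.

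The definition adds a second source of variation. An event that is noxious or undesirable can nearly always be called potentially harmful, so the criterion removes most of the distinction between an AE and an SAE.

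Harm matters in this trial. Section IX.A.2 names risks specific to the experimental arm: distress from recalling earlier coercion, and the unsettling effect that meeting a peer-worker may have. Section IX.A.3 judges the balance of benefit and risk favourable, and VI.F.4 looks ahead to wider use. A harm summary that depends on local reading would support those statements poorly.

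**Working it through.** Whether the rules conflict is a matter of text. Arithmetic enters only in step 4, to size the ambiguity over admissions.

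**1. The two routes side by side**

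| | SAP VI.E.3, later sentences | Protocol IX.C and opening of VI.E.3 |
|---|---|---|
| Recipient | Sponsor | Institution's internal system |
| Deadline | 48 hours | None stated |
| Clock starts | At occurrence | Not stated |
| CRF entry | Yes | Not mentioned |
| Scope | Rests on an AE definition that ignores relatedness | Procedure for SAEs linked to healthcare in the institution |

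The scopes differ as well as the recipients. No section ranks one rule above the other.

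**2. The clock.** Counting from occurrence means that the limit can expire before anyone in the trial knows of the event. Interviewer visits after baseline are at 6 and 12 months (VI.A.3). The investigator is the referring psychiatrist (V.A) and may learn of events between those visits, so the limit can sometimes be met.

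**3. The definition.** The four specific criteria set a threshold. The potentially-harmful criterion sets none beyond the AE definition itself. The criterion on medical accuracy has no clear meaning as worded.

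**4. Admissions.** Hospital admission is not among the SAE criteria and is not exempted either. Section I.B says that involuntary admission can damage patients, so one investigator could reasonably call it potentially harmful and another could leave it out. Inputs from VI.C.1: 400 patients, taken as 200 per arm; 42.6% admitted involuntarily within 12 months in usual care; a 30% reduction; 10% lost to follow-up.

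- Usual care: 200 × 0.426 = 85.2.
- PAD arm: 0.426 × (1 − 0.30) = 0.2982, and 200 × 0.2982 = 59.6.
- Total: 85.2 + 59.6 = 144.8, about 145 of 400 (36%).
- With 10% lost in each arm and their events unseen: 0.90 × 144.8 = about 130.
- With no loss and no effect: 400 × 0.426 = about 170.

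So roughly 130 to 170 patients could be SAE cases or not by local reading. Voluntary and somatic admissions would add to this; the documents give no rate for them.

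**5. What could correct it later.** The assessment table in VI.A.3 has no adverse-event row. The monitoring level in IX.B.4 is minimal and centres on consent forms and the note of participation. Section VI.E.3 specifies no safety analysis and no tabulation by arm. None of these would make the counts uniform.

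**The case against.** The strongest reply is that the two sections can be obeyed together. IX.C does not forbid telling the sponsor; it says only that there is no trial-specific vigilance on the sponsor's side, and the sponsor keeps quality monitoring (VI.E.3, IX.B.4). Nothing in IX.C cancels the CRF instruction. This stands: the duties are not mutually exclusive, and the fair statement is that SAE data may differ, not that they will.

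A reader might infer that the conflict over routes biases the comparison of arms. The documents do not support that. Patients are individually randomised (VI.A.1, VI.B.2), so an investigator can have patients in both arms under the same local rule. The conflict can separate sites and investigators, but gives no reason for arms within a site to diverge. The PAD arm does have peer-worker contacts, but that is a different matter, and VI.C.2.3 foresees informal interviewer meetings under a heading about usual care. The direction of any net difference is unknown.

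A reader might also infer that the arms cannot be compared for harm at all. That goes too far. Somatic, psychiatric and addiction-related hospital stays and emergency visits are collected at baseline, M6 and M12 in both arms (VI.A.2 and VI.A.3), and involuntary admissions are cross-checked against PMSI data.

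Finally, safety is not a listed outcome and the trial is classed as minimal risk. That limits the weight of the point but does not remove the need to align the text.

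**Conclusion.** The point holds as an inconsistency in the reporting rule combined with an SAE definition that lacks a usable threshold. The consequence is that SAE counts may differ between sites and investigators. Its size cannot be computed, because the documents give no SAE rate and no figure for completeness of reporting. The one part that can be sized is the status of involuntary admission, which concerns about 145 patients on the planning assumptions. That figure assumes equal arms, the protocol's 42.6% rate and its 30% effect; it measures ambiguity and does not forecast SAEs.

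The primary efficacy analysis is untouched. The conclusion assumes that no site instruction outside these documents already settles the route. It is worth correcting because the remedy is cheap and VI.E.3 at present contains no analysis of the events it collects.

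**What to change.** 1. Reconcile VI.E.3 and IX.C into one rule for all sites that states the recipient and the deadline. Which route to keep is for the sponsor to decide. Count the deadline from when the investigator learns of the event.
2. Narrow the potentially-harmful criterion and reword the one on medical accuracy so that its meaning is clear. Keep room for the investigator's judgment on unforeseen events.
3. State whether hospital admissions, including involuntary ones, count as SAEs.
4. Ask the same SAE item at M6 and M12 in both arms, record it in the eCRF and add it to the assessment table.
5. State in VI.E.3 that SAEs will be tabulated by arm.

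The cost is an edit to protocol and SAP wording and one eCRF item at two visits that already take place. The downside is slightly more data entry.

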## **4. Sensitivity Analyses**

As a sensitivity analysis, the regressions will be repeated including random effects for sites, and adjusted hazard/odds ratios will be provided based on potential un-balanced baseline characteristics or relevant covariates (such as diagnosis and age). Known or expected associations with the primary outcome variable in our study will be on the basis of previous evidence (e.g. previous publications) and/or on clinical grounds.

Sensitivity analysis will be carried out to address uncertainty around the cost-utility ratio. One-way sensitivity analysis and tornado diagram will be performed to identify thresholds for factors

influencing the ICUR. Probabilistic sensitivity analyses, using the non-parametric bootstrap method, will be carried out to generate mean expected ICURs and to determine whether uncertainty or variation in the data used affect the ICURs. In addition, cost-effectiveness acceptability curves will be drawn to represent decision uncertainty surrounding cost-utility estimates.

## 5. Other analyses

NA

## 6. Handling of Missing Data

Missing data will be handled where possible using multiple imputations or other method according to the type of missing data.

## 7. Interim, Final Analyses and Timing of Analyses

No interim analysis scheduled.

## ***F. Qualitative assessment***

The guiding principle of the qualitative section is better theoretical and practical understanding of recovery processes.

Recovery has been conceptualized by American scientists as a singular process that is not only biological but also social, civic and existential (38). For them, *recovery* concerns not only the course of illness but also the course of life and particularly restoring social ties and the person's autonomy. In this line of action, our approach consists in understanding the forms of life and the specific processes that enable a person to hold on while going through life's challenges and mental illness, and this, whatever the manner they are externally defined in. Particular attention will be paid to representations and awareness of rights (87,88) of the different actors involved in the recovery process.

In synergy with the randomized trial, social anthropology research scientists will purposely place themselves in a perspective of triangulation. Triangulation of data enables to add depth to the collected points of view by revealing new facets of the phenomenon under study and trying to take into consideration the *changing dimension of encountered problems*. This triangulation consists of collecting data from program operations and accounting for the examination of social dynamics present within its implementation. The qualitative approach attempts to open breaches, tries to account for blanks in order to reintroduce a better understanding of the processes at stake at different levels of reality.

On the one hand, it is to assess the expected effects of the program on the individual beneficiaries and on the other hand, to assess its expected but also unexpected effects on relational and systemic dynamics. This perspective gap, once spelled out further, justifies the importance of choosing differentiated methodologies the best adapted to the goals.

The presentation below is split into three parts. The first part explains the chosen themes of investigation, as well as why they were chosen. The second part presents methodology retained for these themes. Finally the expectations of this research project are described.

## 1. Challenge and presentation of the themes of investigation

What can one expect from legally provided tools from a recovery perspective? For research scientists, professionals, users, politicians, the answers may all be different. From a pragmatic social perspective, the different themes presented below will be honed down progressively as the research progresses: whether it is creating a multidisciplinary discussion within the research team, the reflexivity of professional participants, experimentation and the users' opinions and more broadly the evolution of engaged public action instruments.

Interrogations concern:

- Institutional dynamics implemented around the program;
- discussions about the form of advance directives and their possible contents;
- pathways for care and recovery;
- the participatory dimension.

This research program aims to understand how the three categories involved in each of the themes (institutions, professionals and users), while apparently having expectations on different and sometimes opposite horizons, construct tools for regulation, negotiation in order to make the program "hold up" giving it common social sense. Indeed there is inbuilt tension between these themes; action reference frames, goals and challenges are specific to each of them. The documented assessment of how tensions build up and are released within each theme and between the themes will finally be of assistance in choosing policies for the future spreading of the program. In this way, the qualitative section includes a form of assessment research.

After the final report (quantitative and qualitative parts) we propose to translate the research results into recommendations. The method: local monographs and comparative approach.

The program was implemented at several sites, its qualitative assessment will take place at each of them, which will favor a transversal comparative approach and will account more for local contexts. Comparison will be made possible by using the same tools at each site. Then we shall describe how the issue of transversality will be translated, in the inter-site comparison as well as for the triangulation implemented for the epidemiological part of the survey.

## 2. Methodological tools

On each site, the same methodological tools will be offered, making it possible to question each of the three targeted categories of actors: institutional, field practitioners, helpers and program users. There will be adaptations during the survey in order to adapt the approach to the specificities of each field.

### a. Survey of institutional actors: focus groups and interviews

Interviews are scheduled to get to know the local institutional scene and its history: why is experimentation possible there? What vision of the legal instruments of anticipation do the different actors have (professionals in psychiatry, users, militants, helpers)?

Various actors (psychiatric department, organizations) can be interviewed.

Interviews are the preamble to setting up focus groups. The categories of actors in the focus groups will be determined site by site. Focus group topics will be determined with the participants as the actions progress. The first *exploratory focus group*, acts as the first step to allow topics to emerge that seem pertinent for the participants. After these exploratory focus groups, focus groups will be focused on the questions.

The focus group technique implies the presence of three people, one who organizes the debate in a distanced manner, one who plays the role of peer-worker and refocuses the debate, and one who observes all that is non verbal and sharp interventions which would be missed by the audio tape. One of these people will be a user (position to be defined). There will be a debrief afterwards (of at least one hour).

Focus groups will be taped and transcribed. The meetings will be held once per term. The aim is to go back over dynamics of actors, interactions, short, medium and long-term consequences. Focus groups will also be the privileged means of reaching community expectations, shared by the

participants, faced with this new approach, but also their fears.

For example, if we take Marseille, a focus group could include:

- trial participants
- people who had already had PAD before (ex: during the pilot study by [name]);
- facilitators from the organization Eutopia;
- the peer-worker;

## **b. Survey of field practitioners: interviews, participatory observations and focus groups**

The survey of field practitioners will first be **direct and participatory observation**. This enables to:

- document the conditions of a problematic or promising pathway;
- understand the points of view of the different protagonists;
- propose a descriptive report of coordination and negotiation at the time they take place (cross processes and data with what the actors remember);
- note down consensual or non-consensual logic as it is expressed in action to understand the agreements and disagreements at hand, and vice versa.

Participatory observation requires the definition of “target situations” (interactions between professionals and users, between peer-workers and professionals or users for example, with the consent of the participants) and the frequency of observation.

A regular logbook of the frame of discussion is held throughout the program.

Particular attention will be paid to the scope of problematic and promising situations and the manner in which they are defined.

**Interviews** are scheduled with professionals as the *program progresses*. They will help to discover:

- the actors’ point of view concerning their practices;
  - axiology;
  - praxeology;
  - temporality;
  - resources;
  - obstacles and limits;
  - their assessment of results;
  - evolution of their expectations, etc.

If interviews, and this is where the strength of the complementarity of ethnographic methods lies, are coupled with the direct, enable the measurement of the gaps between speech and practice. It is not about “criticizing” the professionals’ practices, but really and truly about confronting what is at play in daily interactions and which, having become mundane, or even trivial in the eyes of the actors, is often missed in interviews. An interview situation is effectively an artificial social situation, during which the actors are disconnected from their usual social context of enunciation related to their practices. Thus the interview gives access to *praxeology* – speech related to practices – while observation enables to study speech put into action, the actors’ practices. However, this decontextualization which is the basis of an interview, physical -since the actors are not “in place” – but also cognitive and social, make it possible to not be trapped in daily imponderables – also implying for them the possibility of taking the back seat, which brings added data and sense compared to observation alone. Nevertheless, the interview situation, while it allows access to their analysis of situations, practices and values, is at risk, depending on the context, of only normative and artificial speeches.(89).

This is why putting the data collected during the interviews alongside those collected during the observations will be a crucial bet. This is even more important and primordial since we sometimes process “sensitive” issues. (90).

The survey of professionals will also include setting up **focus groups** (Morgan, 1997) with the different psychiatrists in the program, as well as with professionals from the psychiatric emergency

department. The theme of these groups will be *problematic pathways*. They will go back over those which are controversial or cause tension, in order to re-elaborate categories of analysis, go into more depth about strong points but also about detected blind spots. The objective in a culture of participatory action research will be double: document problematic pathways and think about a better adjustment of practical responses. Focus groups will be organized every term by the research scientist.

### c. Survey of users

This is the reconstitution and analysis of the users' **capacity pathways** (91).

This notion takes into account the temporality of civilian life, including both biographic dimensions (physiological, experiential, relational) of life experience, and social regulation by rights, especially in life situations where restrictive, involuntary actions have been lived through. The proposed phases articulate the different issues of legal regulations, like the qualification of facts, putting forward ideal principles, the problem of the applicability of these principles and, finally, that of adapting legal regulations.

Data from 6 individual pathways will be collected per site, i.e. 24 pathways. This will be done on a voluntary basis: if there are more volunteers than desired, we will choose by drawing them from among the candidates proposing their pathways. Thus one person per site per month will be interviewed for the duration of the inclusion period.

Out of these 6 pathways, 4 belonging to the "DaiP" group from each site will be documented. The 2 others will be from the "usual care" group. For the people from both groups, there will be a type of biographic, exploratory interview, in order to collect prior capacity pathways. This first wave of interviews will be used to draw up a series of ideal-typical profiles (92) of people concerned who volunteered to participate in this research. Each person will be interviewed every 6 months over the 12 months of follow-up (i.e. 2 interviews per person).

This method has the advantage of documenting pathways at the different moments of build-up in the program for each of the groups and thus obtain a varied palette of situations.

The term interviews, semi-structured, will be about what the subjects feel, their respective experience of the approach, with the aim to assess a potential evolution of these models, of these ideal-typical figures. Comparing the life experience of people included in the "DaiP" group with the others while experimentation is in progress like this, we should be capable of measuring the subjective effects of the program, *in action*.

A final interview will take place at the end of experimentation, in order to collect, from a participatory perspective, subjective feelings and experiences.

